### 2.6. Analysis

The primary goal of the analysis will be to evaluate research objectives 1 and 2. For research objective 1, demographic data will be compared for the intervention and active comparison group. Time-to-event analysis will be used to compare the outcomes between these groups. We also will compare the total number and timing of blood pressure readings. For research objective 2, the analysis will focus on the mediation effects of social identification on health equity. Figure 4 illustrates the planned analyses for the primary outcome.

#### 2.6.1. Research Objective 1

##### Independent Variables and Covariates

The independent variable of interest will be a group variable. Participants will be randomized to one of two groups: the intervention group (digital platform with RBPM) or active comparison (digital platform, no RBPM). The covariates will be the age at enrollment in years, race, ethnicity, health insurance type (e.g., Medicaid, commercial, HMO), gestational age at first visit, and total number of prenatal visits. 

Demographic data will be summarized using means and standard deviations for continuous variables and frequencies and percentages for categorical variables. 

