### 2.3. Planned Analysis: Time to Diagnosis of Hypertensive Disorders of Pregnancy

A planned analysis will be conducted, with the aim of completing the research objectives, sequentially in two phases. The first research objective will be completed as phase 1 using a time-to-event strategy and intent to treat. In this phase, we will evaluate the days to diagnosis of HDP when using the digital platform, with an active comparison group. The comparison group will receive a digital platform that offers educational content but not RBPM. Patients will be assigned 1:1 using a random number generator to either the intervention (digital platform plus RBPM) or active comparison (digital platform). The hypotheses are the following:Diagnosis of previously unrecognized chronic hypertension will increase with use of RBPM.RPBM and use of the digital platform will decrease the days to diagnosis of HDP.RBPM will decrease the time to diagnosis for all users regardless of demographic characteristics.

When phase 1 is completed, our team will incorporate culturally responsive social identification strategies to increase the engagement among Black patients. The content for cultural tailoring will be developed during phase 1 under a separate protocol not described here. The second research objective will be achieved by evaluating this tailoring in a randomized controlled trial as a second phase. The hypotheses are the following: Cultural tailoring will promote social identification and mediate treatment effects on the time to diagnosis of HDP among Black users, narrowing the equity gap in outcomes.Cultural tailoring will improve the perceived quality of care, reduce stress, and improve social support. These benefits will result in additional improvements in perinatal outcomes, such as fewer preterm birth and depression symptoms.

We further anticipate that social identification will create a consistent “brand” for the program (common desirable features, consistent imagery, look and feel) and will affect the time to diagnosis of HDP outcomes [38]. Recognition of the intervention and its tailored features will promote engagement and participation.

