### 2.4. Outcome Measures

The planned primary outcome is the time to diagnosis of HDP. Planned secondary outcomes include an improvement in the perceived quality of care and reduced maternal stress. Additionally, we will measure the effect of cultural tailoring and its associated impact on health equity. While this study is not powered to detect differences in the rates of severe maternal morbidity, we will evaluate this outcome as an investigational hypothesis. 

We have selected biometric, behavioral, and social identification measures that are linked to our conceptual framework and hypotheses. EHR review will provide information on the diagnosis and timing, gestational age at delivery, mode of delivery, maternal comorbidities, and participation in postpartum care. The study instruments will be applied after consent and before enrollment, during pregnancy as specified, and at six to eight postpartum.

Blood pressure. Blood pressure will be taken using the internet-enabled blood pressure equipment provided, which will be linked to the digital platform and integrated with the EHR. These devices are calibrated and tested for consistency with hospital-based medical equipment. All recorded values will be included from the first prenatal visit to 8 weeks postpartum for research objectives 1 and 2. 

Laboratory values. The results of laboratory testing used to diagnose preeclampsia will be extracted from the EHR, including the complete metabolic panel, urine protein–creatinine ratio, and other data for research objectives 1 and 2. 

Quality of Prenatal Care Questionnaire [39]. The QPCQ is a reliable and validated instrument developed to assess the perceived quality of prenatal care. Reported Cronbach’s alpha = 0.96 and inter-item correlation coefficient = 0.88. This will be completed once each trimester for research objectives 1 and 2. 

Perceived Prenatal Maternal Stress Scale (PPNMSS). This validated instrument consists of 28 items organized as four sub-scales of perceived social support, pregnancy-specific concerns, intimate partner interaction, and economic matters [40]. Cronbach’s alpha = 0.83, with an inter-item correlation coefficient of <0.9. For research objectives 1 and 2, the PPNMSS will be completed once each trimester. 

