### 2.5. Sample Size and Recruitment

The sample size was calculated using PROC POWER in SAS for a two-sided Score test in the Cox proportional hazard regression of the time to diagnosis of an HDP in the study group, with a binary variable taking on the values of intervention (digital platform plus RBPM) or active comparison (digital platform). The proportion of total participants in the intervention group was set at 50%. A hazard ratio of 1.4 for the study group was used as the effect size. The overall probability that a participant would be diagnosed with an HPD was set at 15.9% [43]. The total number of subjects needed to achieve a power of 80% with a significance level of 0.05 was determined to be 1745. 

Overall, HDP affects 15.9% of delivery hospitalizations in the US [43], and the prevalence is higher among patients served by the study site. In 24 months, our system provides prenatal care to over 3000 patients. Given this patient volume and prevalence, we considered the estimated sample size feasible with a 60% enrollment rate, which is consistent with the engagement with prior research studies in our setting of similar durations. We anticipate that the required cohort for each research objective will be enrolled within the desired timeline. The total active participant enrollment time for the planned protocol will be a total of 48 months: 24 months for phase 1, and 24 months for phase 2. 

All people presenting at the study site for prenatal care will be invited to participate at their initial prenatal visit by a study research coordinator. Individuals younger than 18 years will be excluded. Over 35% of patients receiving prenatal care at our facility identify as Black, which will allow us to test for the desired sub-group effects related to social identification. Randomization will occur at the time of enrollment, and baseline measures will be completed. Participants will receive USD 25 at the time of enrollment and each time they complete study data collection (enrollment, and then each subsequent trimester and postpartum) in recognition of the additional time required to complete these study materials. Survey data will be compiled using REDcap 14.2.1, a software distributed by Vanderbilt University in Nashville, Tennessee, United States, for non-commercial secure survey data collection, at enrollment and the subsequent timepoints.

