##### Objective 1.A and Analysis Plan

The primary outcome will be the days to diagnosis of an HDP, where an HDP is defined as gestational hypertension, preeclampsia, or preeclampsia with severe features. The days to diagnosis of an HDP will be calculated from the date of the first prenatal visit to the date of diagnosis (ICD-10-CM), clinical problem list (SNOMED-CT), and Intelligent Medical Objects (diagnosis and problems). A patient will be considered censored if they are never diagnosed with an HDP. A Cox proportional hazards regression will be used to model the effect of using the digital platform plus RBPM (intervention) compared to the digital platform alone (active comparison) on the days to HDP diagnosis. The regression coefficients and respective *p*-values, and the hazard ratios with confidence intervals will be reported. The predicted survival curves for each group will be plotted, along with the median days to diagnosis for each group. 

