### 2.7. Data Approach

This study will use data both from the digital platform and the health system’s enterprise EHR. To support the cohort definitions for the randomized trial, digital platform users will be identified by a combination of referrals ordered through the Computerized Physician Order Entry (CPOE) system, matching of contributor systems (i.e., patients with RBPM integration), and industry-standard deterministic matching algorithms. Additionally, the team will use the ICD-10-CM (diagnoses), SNOMED-CT (problems), and Intelligent Medical Objects (diagnosis and problems) coding standards to identify the conditions of interest to support both the time to diagnosis outcome measurements. 

Digital platform data will consist of both manual and automatic data feeds, which will be matched using the approach outlined above. These RBPM readings will be aggregated, and user activity analysis will be aggregated and analyzed with temporal analysis using a multi-paradigm programming language. The number of blood pressure readings and user activity will be correlated with the information in the medical record to establish the relationship between engagement and outcomes. 

Many variables will be defined using EHR data recorded during perinatal care, including demographics, EPDS scores, utilization/engagement, and documentation from the delivery event. These heterogenous data elements are stored in the EHR as structured data to facilitate clean data extraction. They include diagnostics (e.g., lab orders), observations (e.g., vital signs), assessments (EPDS), and medical history (prior diagnoses and chronic conditions). 

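### The primary Cox model's covariate list omits first-visit blood pressure, forgoing an assumed 0.3 to 8 points of power; the test itself stays valid

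*Protocol article*

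**What the plan says.** Under Research Objective 1, the section Independent Variables and Covariates gives the adjustment set: "The covariates will be the age at enrollment in years, race, ethnicity, health insurance type (e.g., Medicaid, commercial, HMO), gestational age at first visit", plus total prenatal visits. The Objective 1.A analysis plan then states "A Cox proportional hazards regression will be used to model the effect of using the digital platform plus RBPM (intervention" against the platform alone, and adds no further covariate. The event is a coded diagnosis, "where an HDP is defined as gestational hypertension, preeclampsia, or preeclampsia with severe features", counted in days from the first prenatal visit.

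Section 2.5 bases the sample size on a "two-sided Score test in the Cox proportional hazard regression" with one binary group variable, and concludes: "The total number of subjects needed to achieve a power of 80% with a significance level of 0.05 was determined to be 1745". Women are invited at their initial prenatal visit and randomised on enrolment. On allocation, section 2.3 says: "Patients will be assigned 1:1 using a random number generator to either the intervention (digital platform plus RBPM) or active comparison (digital platform".

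Two places bear on whether a baseline value exists. Section 2.7 lists the structured EHR elements: "They include diagnostics (e.g., lab orders), observations (e.g., vital signs), assessments (EPDS), and medical history (prior diagnoses and chronic conditions". Section 2.4 says of blood pressure: "All recorded values will be included from the first prenatal visit to 8 weeks postpartum for research objectives 1 and 2", but the text just before it concerns the connected study device.

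**The concern.** Gestational hypertension and preeclampsia are conditions of raised blood pressure, so the pressure at time zero is a natural candidate predictor. The plan adjusts for insurance type and ethnicity but not for this. Only people under 18 are excluded, so starting pressures may vary widely.

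In a Cox model, leaving out a prognostic covariate pulls the estimated hazard ratio towards 1, and chance differences between arms on that covariate remain in the estimate as noise. At stake is some power in a trial that plans for 80% and states no margin above it. The choice also has to be made before outcome data are seen, because adding the covariate later would look data-driven.

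**Working it through.** **Inputs from section 2.5:** hazard ratio 1.4, event probability 15.9%, half of participants in each arm, two-sided 0.05, power 80%, total 1745.

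**1. The plan's own figure.** Events needed for the Cox score test:

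D = (1.960 + 0.842)² / (0.25 × ln(1.4)²) = 277.3

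N = 277.3 / 0.159 = 1744.1, rounded up to 1745. This matches, and power at 1745 is 80.0%. It is the power of a test with the group variable alone.

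**2. Effect of adding blood pressure.** The documents give no prognostic strength, so it is assumed over a range. Trials of 1745 women were simulated with 1:1 allocation, exponential hazards, administrative censoring, 15.9% events and a standard-normal baseline covariate acting log-linearly (6000 runs per row). A Cox model was fitted with and without the covariate. The article does not say whether 1.4 is the unadjusted or the adjusted hazard ratio, so both readings are shown.

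| Assumed HR per SD | 1.4 is unadjusted (approx.): power without / with | Gain (points) | 1.4 is adjusted: power without / with | Gain (points) |
|---|---|---|---|---|
| 1.3 | 78.8% / 79.2% | 0.3 | 78.6% / 79.1% | 0.5 |
| 1.5 | 79.7% / 80.6% | 0.9 | 77.2% / 78.7% | 1.5 |
| 2.0 | 79.7% / 83.2% | 3.5 | 74.4% / 78.6% | 4.2 |
| 2.5 | 79.8% / 85.3% | 5.5 | 71.0% / 78.6% | 7.6 |

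Gains are taken from unrounded powers. Under the second reading, the average hazard ratio from the model without blood pressure is 1.395, 1.392, 1.377 and 1.359 down the rows, which shows the pull towards 1. When the covariate has no effect, adjusting costs nothing material (78.9% without, 78.8% with).

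**3. Validity.** With no treatment effect (8000 runs per setting), type I error was 4.7% to 4.9% without blood pressure and 4.8% to 5.1% with it.

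**4. Chance imbalance.** The SE of the difference in mean baseline pressure is √(4/1745) = 0.048 SD, so 95% of trials fall within 1.96 × 0.048 = ±0.094 SD. At that limit the log hazard ratio shifts by 0.094 × ln(HR per SD), a factor of 1.02, 1.04, 1.07 or 1.09 for the four strengths. The SE of the log hazard ratio is about 2/√277.3 = 0.120, so the shift is 0.2 to 0.7 of one SE.

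**5. Shape of the relation.** Objective 1.B treats newly diagnosed chronic hypertension before 20 weeks as a separate outcome. Women with the highest first-visit values may therefore be coded there and not have the primary event. A simulation of this, assuming a log hazard of −1 for the top 5% to 10% of pressures and an adjusted hazard ratio of 1.4 (1500 runs per setting, error about 1 point), gave these gains from a linear term:

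- HR 2.0 per SD: 0.4 to 0.5 points, against 2.9 with log-linear risk.
- HR 2.5 per SD: 0.8 to 1.8 points, against 7.3 with log-linear risk.

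**The case against.** The strongest case against is that nothing here is wrong. The sample size is correct for the test it describes. If 1.4 is the unadjusted hazard ratio, planned power is met and blood pressure could only add to it. That stands. A reader might infer from the 71% to 77% entries that the trial is underpowered. Those entries require 1.4 to be the blood-pressure-adjusted hazard ratio, which the article does not say.

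A reader might also infer that chance imbalance biases the comparison. It does not: randomisation keeps the test valid, and the confidence interval already allows for the shifts in step 4. Nor can the allocation be called unrestricted. The article mentions only a random number generator, and stratification is a detail that a condensed article may leave to the full protocol.

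On availability, no sentence promises a first-visit value for every woman. The section 2.4 statement concerns the study device, which the comparison arm may not have. Support comes from section 2.7 together with enrolment at the initial visit. That makes a clinic value in both arms likely, but it guarantees neither completeness nor timing.

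Finally, the size is assumed. The simulations contain no other covariate, so any overlap with age, race, insurance or gestational age is not deducted. The event is a coded diagnosis that also depends on detection and laboratory results, and risk may not be log-linear in pressure. All of this reduces the gain. None of it reverses the direction, and no simulation showed a material loss from adjusting.

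**Conclusion.** The concern holds as a modest efficiency point. The covariate list leaves out a likely prognostic baseline value that the trial's own data sources should hold in both arms. The randomised comparison is valid without it, and 1745 and 80% are right for the unadjusted test.

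The forgone gain is about 0.3 to 1.5 points for assumed hazard ratios of 1.3 to 1.5 per SD, and about 3.5 to 8 points for 2.0 to 2.5. These figures assume log-linear risk and no overlap with the listed covariates. If either assumption fails, expect the low end.

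**What to change.** In Independent Variables and Covariates under Research Objective 1, add first-visit blood pressure to the primary Cox model as a continuous covariate:

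- **Source:** the clinic value recorded in the EHR at the first visit, before randomisation, in both arms. Do not use the study cuff.
- **Form:** a flexible function such as a restricted cubic spline, because women with the highest values may be coded as chronic hypertension. Its gain was not simulated here.
- **Missing values:** a simple rule stated in advance, for example single imputation with a missing indicator.
- **Reporting:** label the hazard ratio as covariate-adjusted (conditional).

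The cost is a short change of wording, made before outcome data are seen, and one field from a data source already in use. No extra patients or procedures are needed. The downsides are that the hazard ratio becomes conditional on baseline pressure and that some first-visit values may be missing.

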## 2. Proposed Methods

### 2.1. Conceptual Model and Approach

The selected digital technology with RBPM improves the availability of key biometric values for expectant and birthing individuals who face barriers to care and have trouble navigating healthcare systems. Patients using the app send blood pressure readings to a digital platform integrated with their electronic health record (EHR), which increases the cadence of blood pressure reading and monitoring, and offers the potential to identify HDP earlier. The digital platform also provides a library of educational resources and media to the user. The app is designed to increase patient engagement with care, reduce access barriers, and facilitate patient–physician/patient–midwife connectivity between prenatal office visits. 

Figure 1 presents our conceptual framework and study objectives. We hypothesize that providing patients with RBPM through the selected technology will moderate prenatal care effects on the time to diagnosis of HDP, reducing maternal morbidity and mortality associated with the condition. Social and environmental variables, including stress, will moderate the effects. We further hypothesize that introducing cultural tailoring will mediate the desirability of engagement with RBPM, and that adherence to care plans will promote greater equity among users. 

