### 2.2. Intervention Selection and Features

Multiple options for RBPM and pregnancy applications exist. Our team selected this platform because it aligned with several project goals. For instance, it offers integration with the EHR and the use of an internet-enabled, electronic blood pressure cuff that automatically populates values, reducing the patient burden, and expediting access to blood pressure values. Integration of the digital platform with our EHR also facilitates seamless enrollment without an additional strain on staff resources. Enrollment occurs by placing a single order from the EHR, making it as easy to connect the patient to the platform as any other clinical order related to patient care. The selected platform also offers continuous monitoring of RBPM values (twenty-four hours a day, 365 days a year) and allows providers to select blood pressure targets aligned with the individual patient risk status. Figure 2 defines blood pressure targets by risk status. 

Abnormal lab values are relayed to the physician or midwife for immediate triage. This feature delivers blood pressure readings outside identified ranges for the patient’s risk profile to the healthcare team, allowing for real-time intervention. Figure 3 illustrates the communication sent to users with abnormal blood pressure readings, which are automatically sent to the healthcare team for follow-up. 

The educational content is inclusive of a range of colors and textures for skin and hair, and includes social identities that are underrepresented in electronic applications and avatars. Furthermore, the written content offers the ability to adjust for different reading levels and avoid confusing idioms. This feature was essential to our selection as we serve many patients with low reading levels and use of English as a non-dominant language. Additionally, the media offers closed-caption capabilities, and an option to access the content in Spanish is available. Importantly, these flexibilities are extended to in-app text messaging sent directly to patients. were important, the ability to further customize content facilitates cultural tailoring and supports objective two.

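### The covariate lists for both objectives include total prenatal visits, a post-randomisation quantity; adjusting for it means the group coefficient need not estimate the intent-to-treat effect

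*Protocol article*

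**What the plan says.** In the protocol article, 2.6.1 (Independent Variables and Covariates) lists the objective 1 covariates as age, race, ethnicity, insurance type, "gestational age at first visit, and total number of prenatal visits". Section 2.6.2 repeats the list for objective 2. All the items are baseline characteristics except the last.

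Four other statements matter:

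- **Timing.** Under 2.5, patients "will be invited to participate at their initial prenatal visit by a study research coordinator", and "Randomization will occur at the time of enrollment, and baseline measures will be completed".
- **Primary outcome and model.** Under Objective 1.A, "The days to diagnosis of an HDP will be calculated from the date of the first prenatal visit to the date of diagnosis", analysed by Cox regression on study group.
- **Analysis principle.** Section 2.3 describes phase 1 as "using a time-to-event strategy and intent to treat".
- **Purpose of the platform.** Section 2.1 states: "The app is designed to increase patient engagement with care, reduce access barriers". Section 2.2 says of abnormal readings: "This feature delivers blood pressure readings outside identified ranges for the patient’s risk profile to the healthcare team, allowing for real-time intervention".

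Nothing in the article restricts the count to visits before randomisation, treats it as time-dependent, or confines it to a sensitivity analysis.

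**The concern.** An intent-to-treat comparison may be adjusted for variables fixed before randomisation. The visit total is not one of them, and it raises a separate difficulty in each model.

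- **Possible mediator.** A platform meant to raise engagement, with alerts that prompt follow-up, may add visits, or remote readings may replace some. Adjustment would then remove or distort part of the effect under test.
- **Possible consequence of the outcome.** A diagnosis of HDP may change later follow-up and the date of delivery, and so the total.
- **Future information.** A Cox model compares the participant diagnosed on a given day with everyone still at risk on that day. A whole-pregnancy total gives all of them values that include visits not yet made.
- **Objective 1.B.** The outcome is new chronic hypertension before 20 weeks, but the total also counts visits after that window.
- **Objective 2.** The outcome is the number of recorded blood pressure readings. Visits may lie on the path from tailoring, through engagement, to readings.

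At stake is the primary result: the reported hazard ratio could be too low or too high, and the data would not show which.

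**Working it through.** **Step 1. The plan's own sample size.** Inputs from 2.5: hazard ratio 1.4, 1:1 allocation, two-sided 0.05, power 80%, event probability 0.159. By Schoenfeld's formula:

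- Events = (1.960 + 0.842)² / (0.25 × (ln 1.4)²) = 277.3
- N = 277.3 / 0.159 = 1744.1, rounded up to 1745

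This matches the stated figure. The only model term it uses is the study group, so dropping a covariate leaves N unchanged.

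**Step 2. Timing.** Approach at the first visit and randomisation at enrolment leave at most the visits up to enrolment before randomisation. The rest of the total comes later and, for cases, some of it after the event.

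**Step 3. Size, by simulation.** The article gives no visit schedule, so both visit patterns below are assumptions. N = 1745 in each.

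- *Simulation A* (600 trials per scenario): visits every 4, then 2, then 1 weeks; two per week after diagnosis; delivery at 37 weeks or soon after diagnosis; about 17% diagnosed. The Cox model has group and gestational age at first visit, with or without total visits.
- *Simulation B* (500 trials per scenario): about 11 visits over about 200 days; up to 8 extra visits, pro rata to the time left after diagnosis; a shared risk factor; about 15.9% diagnosed. The Cox model has group, with or without total visits.

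| True HR | Average visit difference, RBPM minus comparison | Simulation | HR with visits in model | Rejection rate |
|---|---|---|---|---|
| 1.0 | none | B | 1.00 | 6.8% |
| 1.0 | about +1 | A | 0.80 | 52% |
| 1.0 | +1.2 | B | 0.74 | 68% |
| 1.0 | about −1 | A | 1.26 | 49% |
| 1.0 | −1.0 | B | 1.34 | 66% |
| 1.4 | no direct arm effect | B | 1.34 | 66% |
| 1.4 | +1.4 | B | 1.00 | 5% |
| 1.4 | −0.8 | B | 1.81 | 100% |

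Without visits in the model, B gave type I error of 4.4–6.4% and, at true HR 1.4, an HR of 1.38–1.40 with 75–80% power. In the row with no direct arm effect, the model without visits gave 1.39 and 75%.

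The 6.8% in the first row is compatible with 5%: the Monte Carlo standard error is √(0.05 × 0.95 / 500) = 1.0 percentage point.

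**Step 4. Why the figures come out this way.** In A the fitted hazard ratio per extra visit was about 1.25, because diagnosis adds visits. If the arm shifts the mean by one visit, the group coefficient has to offset that: 1.0 / 1.25 = 0.80 for a visit added, and 1.0 × 1.25 = 1.25 for a visit removed. The simulated values are 0.80 and 1.26.

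The modest loss at true HR 1.4 without a direct arm effect has a similar source. More diagnoses in the RBPM arm bring more post-diagnosis visits (0.23 on average in B), and the covariate absorbs part of the effect.

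**Limits.** All the shifted scenarios assume both links: arm to visits, and diagnosis to visits. Power figures from A are not used, because its power without the covariate was 89% against the plan's 80%. One extreme B scenario (true HR 1.4, about four visits added) had non-converging fits and is left out. Objectives 1.B and 2 were not simulated.

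**The case against.** The best case for the covariate is that visits measure the opportunity to be diagnosed, so adjustment levels that opportunity. Randomisation already balances opportunity at baseline, however, and any difference that arises later may be part of the effect. Four further objections deserve an answer.

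1. **The models are not written out.** Objectives 1.A, 1.B and 2 name the group (and, for objective 2, race interactions) but not the adjustment terms, and the sample size rests on group alone. This is fair, but a covariate list placed directly ahead of the models has one natural reading. A fuller analysis plan would have to reverse it, not merely fill a gap.
2. **No section says that RBPM or a diagnosis changes the number of visits.** This stands. A reader might infer that visits are definitely caused by both. Section 2.1 speaks of contact between office visits, and 2.2 of triage and follow-up without naming an extra visit. The text supports only that an effect is plausible.
3. **The harm may be small.** This also stands. With no arm effect on visits, the bias is nil under the null and modest at 1.4. A reader might conclude that the randomised comparison is certainly invalid, or biased in a known direction. Neither follows, since the large errors need an assumed shift in visits.
4. **Objective 2 differs.** A reader might say that the covariate is partly the outcome itself. That holds only if clinic readings are counted. Section 2.4 can be read as covering only the supplied device, and the objective 2 text does not settle it. Both phase 2 arms have RBPM, so the alerts do not separate them. What remains is mediation through engagement, which tailoring is meant to raise.

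**Conclusion.** The point holds as a fault in a stated choice. The visit total is a post-randomisation covariate in both lists, and adjusting for it is at odds with the declared intent-to-treat comparison.

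The possible error in the primary hazard ratio runs from nil or modest, if visits do not respond to the arm, to large. A shift of about one visit on average moves a true 1.0 to about 0.74–0.80 or 1.26–1.34, with false rejection of roughly 50–70%. These figures rest on assumed visit patterns, including extra visits after diagnosis, and on the covariates entering the models as listed. The actual size and direction cannot be known from the article.

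It should be corrected before analysis, because the primary result should not depend on an engagement intervention leaving use of care unchanged. For objective 1.B and objective 2 the conclusion is qualitative.

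**What to change.** Delete the prenatal-visit total from the covariates of the models in 2.6.1 and 2.6.2, and keep the baseline covariates already listed. Report visit counts by arm descriptively, or use them in a separate analysis labelled as mediation.

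No replacement covariate is needed. If more baseline adjustment is wanted, 2.7 already lists prior diagnoses, chronic conditions and vital signs among the EHR data, but that is optional and only values recorded before randomisation should be used.

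The cost is one term removed from two lists. No new data are needed, and the sample size stays at 1745.
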